**8. Work plan and study timeline**

| **ACTIVITIES**  *Lead Agency* | **STUDY TIMELINE** | | | | | | | | | | | | | | | |  | | | |
| --- | --- | --- | --- | --- | --- | --- | --- | --- | --- | --- | --- | --- | --- | --- | --- | --- | --- | --- | --- | --- |
| **2015** | | | **2016** | | | | | | | | | | | | |  | | | |
| *Summer* | *Fall* | *December* | *January* | *February* | *March* | *April* | *May* | *June* | *July* | *August* | *September* | *October* | *November* | | *December* |  | | | |
| Local ethics committee review  *MoHS* |  |  |  |  |  |  |  |  |  |  |  |  |  |  | |  |  | | | |
| Investigators coordination meeting  *MoHS* | **X** |  |  |  |  |  |  |  |  |  |  |  |  |  | |  |  | | | |
| Independent Data Monitoring Committee (IDMC) initial discussions  *MoHS* |  |  | **X** |  |  |  |  |  |  |  |  |  |  |  | |  |  | | | |
| Questionnaire development & completion  *WHO/US-CDC* | **X** |  |  |  |  |  |  |  |  |  |  |  |  |  | |  |  | | | |
|  | **2015** | | | **2016** | | | | | | | | | | | | |  | | | |
|  | *Summer* | *Fall* | *December* | *January* | *February* | *March* | *April* | *May* | *June* | *July* | *August* | *September* | *October* | *November* | *December* | |  | | | |
| Training on participant recruitment  *MoHS/WHO/US-CDC* | **X** |  |  |  |  |  |  |  |  |  |  |  |  |  |  | |  | | | |
| Training on informed consent process  *MoHS/WHO/US-CDC* | **X** |  |  |  |  |  |  |  |  |  |  |  |  |  |  | |  | | | |
| Training on administering questionnaire  *MoHS/WHO/US-CDC* | **X** |  |  |  |  |  |  |  |  |  |  |  |  |  |  | |  | | | |
| Recruitment for pilot | **X** |  |  |  |  |  |  |  |  |  |  |  |  |  |  | |  | | | |
| Data collection for pilot | **X** | **X** | **X** | **X** | **X** | **X** | **X** | **X** | **X** | **X** | **X**  ***Last projected 6 month follow up visit*** |  |  |  |  | |  | | | |
|  | **2015** | | | **2016** | | | | | | | | | | | | |  |  |  | |
|  | *Summer* | *Fall* | *December* | *January* | *February* | *March* | *April* | *May* | *June* | *July* | *August* | *September* | *October* | *November* | *December* | |  | | | |
| Data analysis for pilot | **X** | **X** | **X** | **X** | **X** | **X** | **X** | **X** | **X** | **X** | **X** | **X** |  |  |  | |  | | | |
| Laboratory analysis for pilot  *US-CDC, China-CDC* | **X** | **X** | **X** | **X** | **X** | **X** | **X** | **X** | **X** | **X** | **X** | **X** |  |  |  | |  | | | |
| Recruitment for full study |  | **X** | **X** | **X** |  |  |  |  |  |  |  |  |  |  |  | |  | | | |
| Data collection for full study |  | **X** | **X** | **X** | **X** | **X** | **X** | **X** | **X** | **X** | **X** | **X** | **X** | **X** | **X**  ***Last projected 6 month follow up visit*** | |  | | | |
| Laboratory analysis  *China-CDC, US-CDC* |  | **X** | **X** | **X** | **X** | **X** | **X** | **X** | **X** | **X** | **X** | **X** | **X** | **X** | **X** | |  | | | |
| Writing interim project report  *WHO/US-CDC* |  |  | **X** | **X** |  |  |  |  |  |  |  |  |  |  |  | |  | | | |
|  | **2015** | | | **2016** | | | | | | | | | | | | |  |  |  |  |
|  | *Summer* | *Fall* | *December* | *January* | *February* | *March* | *April* | *May* | *June* | *July* | *August* | *September* | *October* | *November* | *December* | |  | | | |
| IDMC interim review |  |  |  | **X** |  |  |  |  |  |  |  |  |  |  |  | |  | | | |
| Writing final project reports  *MoHS / WHO/US-CDC* |  |  |  |  |  |  |  |  |  |  |  |  | **X** | **X** |  | |  | | | |
| IDMC final review |  |  |  |  |  |  |  |  |  |  |  |  | **X** |  |  | |  | | | |
| Final project review process  *MoHS* |  |  |  |  |  |  |  |  |  |  |  |  | **X** | **X** |  | |  | | | |
| Dissemination of project outcomes  *MoHS / WHO/US-CDC* |  |  |  |  |  |  |  |  |  |  |  |  |  |  | **X** | |  | | | |

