Limited evidence suggests that live EBOV can persist in urine for 26 days following symptom onset. Evidence regarding EBOV in vaginal secretions is also limited. EBOV RNA has been detected in vaginal secretions at 33 days after symptom onset; due to the type of diagnostic test used (RT-PCR), it was not clear whether these traces represented live virus. Similarly, EBOV RNA was detected in sweat at 40 days after symptom onset, but no live virus was isolated. In addition, rectal swabs and conjunctival fluid have been found by RT-PCR to contain EBOV RNA at 29 and 22 days after illness onset, respectively. A limited number of saliva specimens have been tested by RT-PCR, all yielding negative results. Sexual transmission has never been definitively documented for EVD, although there have been a handful of anecdotal reports of suspected sexual transmission during the current outbreak.

The risk of sexual transmission of EBOV is not sufficiently documented. Prior to March 2015, guidance from World Health Organization (WHO) and The United States Centers for Disease Control and Prevention (US-CDC) recommend that Ebola survivors should abstain from sexual intercourse for 3 months (90 days) after the onset of symptoms, or use condoms if abstinence is not possible. Data which has emerged during this epidemic includes RT-PCR positive semen at 140 days post symptom onset and a case report of suspected sexual transmission in Liberia (March 2015) from a male survivor one of his female sexual partners (Christie et al., 2015; Mate et al., 2015). The male survivor had RT-PCR positive semen 199 days after symptom onset. Genetic sequencing of the viruses within this suspected transmission chain and limited epidemiological data suggested sexual transmission. Following the publication of this case report, as of 08 May 2015, both WHO and US-CDC updated their guidance on sexual practices of male EVD survivors. The WHO recommendations include abstinence or correct and consistent condom use for *at least* 6 months and for male survivors who have access to testing, to have their semen tested monthly from 3 months onwards; and for those who test positive, monthly thereafter until two consecutive RT-PCR negative results. Published RT-PCR data from the pilot phase of this study demonstrated RT-PCR positive semen samples 9 months after symptom onset ([name] et al., 2015).

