• Counsellors will provide laboratory results only in person and only to participants who (1) return for a follow-up study visit; and (2) present their study ID card or confirm their identity and study ID number; and (3) agree to receive their own results. Individual results will not be shared with anyone other than the study participant. Results will be presented according to the counselling script.

• Virus isolation results from US-CDC Atlanta will be reported promptly to the study PI and entered in the secured data base as they arrive. These confirmatory results will not be available within a clinically relevant time frame (6 months). Positive results will be reported to participants.

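### The final reports and the IDMC final review are scheduled before main-study data collection and laboratory work end, and no data cut-off is stated

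*Combined protocol and SAP*

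**What the plan says.** The timeline table in Section 8 has one column each for summer 2015, fall 2015 and December 2015, then one for each month of 2016. Its rows read as follows.

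- "Recruitment for full study": fall 2015 to January 2016.
- "Data collection for full study": fall 2015 to December 2016, with the December cell marked "Last projected 6 month follow up visit".
- "Laboratory analysis" (both laboratories): fall 2015 to December 2016.
- "Writing final project reports" and the final project review: October and November 2016.
- "IDMC final review": October 2016 only.
- Dissemination: December 2016.

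There is a data-analysis row for the pilot but none for the full study, and no data cut-off is stated.

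On isolation results from Atlanta, Section 6 says: "These confirmatory results will not be available within a clinically relevant time frame (6 months". Section 2.2.1 sets the post-clearance visits at 3 and 6 months after the second negative. Section 2 (Main study) restarts fortnightly testing if one of those visits is positive. Section 7 lists the longest duration of culture positivity in each fluid among the primary measures. Detection 3 and 6 months after clearance is a sub-objective in Section 1.2.1.

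**The concern.** A final report should rest on the completed data set. Here the final report and the IDMC's last look come before the last visits and before the laboratories finish. Culture results, which lag collection by months, fall further behind.

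The missing data are not a random subset. They are the latest specimens, the latest culture results and the 6-month visits of those who cleared last. These bear on two stated outcomes: maximum duration, and positivity 3 and 6 months after clearance. Section 14 says that interim and final results will be used to revise WHO and US-CDC recommendations, so readers need to know whether a stated maximum is complete or provisional.

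**Working it through.** This is calendar arithmetic on the Section 8 table. The December 2016 date for the last 6-month visit cannot be rebuilt forwards, because the protocol gives no assumed clearance time. It can only be worked backwards.

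**1. Order of events.** Data collection and laboratory work end in December 2016. The IDMC final review, in October, is 2 months earlier. Report writing ends in November, 1 month earlier. The pilot rows are in a workable order: collection ends in August 2016, and laboratory work and analysis end in September, before the October reports.

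**2. Culture lag.** Take 6 months as the turnaround. Read literally, Section 6 implies longer. Section 2.2.3 gives six months from receipt as a target, worded for the pilot.

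- October 2016 − 6 months = April 2016, and November 2016 − 6 months = May 2016. Only specimens received by about April–May 2016 would have isolation results in the report.
- A participant enrolled at the end of January 2016, 0–3 months after onset (main-study sample size table), is then (0 to 3) + 3 = 3–6 months past onset in April and (0 to 3) + 4 = 4–7 months in May.
- A specimen received in December 2016 would have its result in about June 2017.

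**3. The 6-month visit.** December 2016 − 6 months = June 2016 as the latest second negative. Counted from the end of January 2016 that is 5 months, or 5–8 months after onset for the 0–3-month cohort. Someone with a second negative in July–September 2016 still has the 3-month visit inside the timeline (September + 3 months = December) but not the 6-month visit. After September, neither fits.

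**4. A case from the plan's own background.** Section 1.1 reports that the pilot "demonstrated RT-PCR positive semen samples 9 months after symptom onset". For a last-enrolled man, 9 months after onset falls between the end of July 2016 (onset 3 months before entry: January + 6) and the end of October 2016 (onset at entry: January + 9).

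- Two negatives at 2- to 4-week intervals add 4–8 weeks, so the second negative comes between about late August and late December 2016. His whole RNA-positive period is therefore sampled inside the data-collection window.
- His 6-month visit falls no earlier than January to April 2017 even before those weeks are added, so it is outside the timeline.

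**5. Retesting.** After a positive in December 2016, two fortnightly negatives take at least 4 weeks, so testing runs to the end of the year or beyond.

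**6. How many late clearers?** The documents give no clearance rate. As an assumption only, let residual clearance among the last-enrolled baseline positives be exponential with median m months. The share still positive after t months is 0.5^(t/m).

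| Median m (months) | June 2016 (t = 5) | September 2016 (t = 8) | December 2016 (t = 11) |
|---|---|---|---|
| 2 | 18% | 6% | 2% |
| 3 | 31% | 16% | 8% |
| 4 | 42% | 25% | 15% |
| 6 | 56% | 40% | 28% |

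The June column approximates the share with no scheduled 6-month visit. The range is too wide to put one figure on the loss.

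**The case against.** A reader might infer that the timeline cuts off the longest persisters, so that maximum duration is biased low and any rebound is missed. The documents do not support that.

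- Follow-up runs until clearance, with no calendar stop (Project summary, Sections 2.2.1 and 2.2.2), and the December date is labelled a projection. The man in step 4 is sampled throughout his positive period. At December 2016 the last 0–3-month enrollees are 11–14 months past onset. Survivors 12–15 months from onset (the tail-end cohort of Section 1.2.4), if enrolled by January 2016, would be at 23–26 months.
- The 9-month figure is RT-PCR. It does not show how long culture stays positive.
- Anyone with a second negative by June 2016 has both later visits inside the window, so only later rebounds are affected.
- Section 2.2.3 excludes main-study semen from Atlanta culture, so the six-month lag is not established for that fluid. Section 2 (Main study) sends every RT-PCR-positive specimen there; these sections must be reconciled.

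All of this stands and limits the point. Two further objections carry less weight. The report row is plural and not labelled pilot or main study, and October–November would suit the pilot; but on that reading the main study has no final report and no IDMC final review scheduled. The planned survival analysis can accommodate right-censoring, but it does not say how a participant still positive enters the reported maximum.

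**Conclusion.** The point holds as a sequencing fault, with high confidence in the order of events. The IDMC final review precedes the end of main-study data collection and laboratory work by 2 months, and the end of report writing precedes it by 1 month. With a six-month turnaround, Atlanta culture results for main-study fluids other than semen would be in the report only for specimens received by about April–May 2016. Second negatives after June 2016 have no scheduled 6-month visit, and retesting after a late-2016 positive has no place in the schedule.

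Loss of the true maximum duration is not shown. That would need positivity beyond the data cut, which the documents neither show nor rule out. What does follow is that a maximum computed on incomplete late data can rise or stay the same when the rest arrives but cannot fall, so at that point it is a lower bound. The conclusion assumes that the schedule is followed as printed and that Section 6's six months applies to the main study. It should be corrected before the final analysis.

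**What to change.** 1. Add a full-study analysis row. Place the main-study final analysis, IDMC final review and final report after the last 6-month visit plus the culture turnaround.
2. Relabel the October–November 2016 report as interim for the main study. Section 14 already foresees interim results informing recommendations.
3. If a calendar cut is kept, state its date in Section 7, treat participants still positive as right-censored, and report the maximum as *at least X days*. Say how many 6-month visits and culture results were outstanding.
4. Reconcile Section 2 with Section 2.2.3 on where main-study semen is cultured, so that the turnaround for that fluid can be stated.

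The cost is a few timeline rows and a short addition to Section 7. The downside is a later final report, softened by the interim one.

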**9. Main problems anticipated and proposed solutions**

Main challenges to the success of the project include willingness of participants to provide biological specimens from sensitive locations and involving masturbation for men, and to share intimate information on sexual behavior. Proposed solutions are to ensure trained interviewers and medical staff of appropriate genders and cultural backgrounds, who are used to discussing sexual behavior, and to take bio-samples of sensitive character. Also to secure an environment where the interviewee will be secure the procedures and information is kept confidential. The ability to provide quick turnaround of specimen processing and analysis for timely report back to participants, especially in the breast milk module will also be a challenge.

**10. Applicability of results**

The results will be of great relevance to provide evidence-based information to circumvent EBOV transmission from patients recovered from EVD. They will inform the development of recommendations used in the current epidemic setting, as well as in future situations with resurgence of EBOV. The inclusion of PLHIVs in the study will allow documentation related to co-infection and potential changes to HIV programming during EVD outbreaks.

**11. Gender considerations**

Both male and female participants will be enrolled in this study.

**11.1 Describe how women and men are affected by the public health need that the study addresses, and whether this is a need expressed or felt by women and /or men**

Both men and women are significantly affected by the EBOV epidemic. Women are likely more vulnerable to the risk of sexual transmission of EBOV, given both their biological vulnerability related to the vaginal mucosa and structural gender inequities that give women limited possibilities to negotiate condom use. Men have been victims of law-enforcement actions in relation to suspicions of sexual transmission of EBOV.

In addition, survivors are reporting the need for reassurance of their status with regard to potentially infectious EBOV and the importance for them to know if they may return to their normal sexual practices.

Additionally, women are also more vulnerable to HIV infection in addition to the aforementioned vulnerability to sexual transmission of EBOV, therefore the inclusion of PLHIV will contribute to the discussion on the differences in public health need between genders.

**11.2 Explain how the research contributes to identifying and/or reducing inequities between women and men in sexual and reproductive health and health care**

The research aims at verifying the persistence of EBOV among both women and men, and to assess associations to suspected sexual transmission of EBOV, and hence aims at providing key-information to both women and men. In addition evidence-based strategies will inform human rights based response to controlling transmission that does not include imprisonment or isolation.

**11.3 Describe measures taken to facilitate the individual participation of women or men in the research process in light of their different life situations**

Recruitment will happen at ETUs and from survivor registries, with enrollment targets that include both men and women. Actions will be taken to ensure both women and men may be interviewed privately and in an environment where they are at ease. Interviewers of the same sex as the participant will secure a place and time of interview that is private and does not interfere with other pertinent activities. Special precautions will be taken to protect survivors where secondary cases occur, in order to avoid a response that is not evidence-and rights-based.

**11.4 Describe measures taken to ensure that community involvement is inclusive**

Explorative focus group discussions with key stakeholders in the community are being proposed. The discussions will focus on community involvement and a needs-based approach. PLHIV support groups located in the community level will also be engaged in identifying PLHIV EVD survivors to approach for recruitment to the study.

**11.5 Describe the sex composition of the research team, and their duties and responsibilities in the proposed research**

The research team comprises both men and women (see above).

**12. Ethical considerations**

**12.1 Study population, recruitment strategy and informed consent process**

• Recruitment to the cohort will take place at the ETUs at the time of discharge or later on via survival registers or clinics; informed consent will be explained by trained research staff at the time of recruitment at the study site.

• All adult (18 years or above) men or women, consecutively discharged or in convalescent care, with a confirmed recovered EVD should hence be informed about the study and invited to participate, providing informed consent in writing (Appendix 1, see Ethics section below) (along Main study).

• Due to the confidential nature of HIV status, PLHIV support groups will be engaged in order to identify and recruit PLHIV EVD survivors. HIV Counselors will also be engaged to encourage newly diagnosed PLHIVs who are also EVD survivors.

**12.2 Perceived risks and benefits of the study, both at the individual and community levels**

The project is dependent on willingness from participants to share intimate information on sexual behavior, and to provide biological specimens. For the individual, there is a risk of the intimate interview and sampling procedure creating anxiety for the interviewee and for his/her family members. Specimen collection may cause discomfort, pain, or local infection (Any invasive specimen collection can have side effects that should be detailed here. In particular, vaginal and rectal swabs can rarely cause local trauma or infection that is usually minor. Study participants receiving their results may cause psychological and social stress, especially when results are of unknown clinical utility and may be subject to misinterpretation. At the community level, there is a risk of stigma or discrimination enacted towards study participants. For PLHIVs, there is a risk of unconsented disclosure of HIV status.

Benefits of the study include possibilities for participants to have information on any viral persistence in body fluids, for the community to get accurate recommendations on how to stop transmission chains. For the HIV sector, a benefit would be an evidence-based understanding of whether HIV affects EVD survivors differently and result in potential changes in programming during EVD outbreaks. Participants will receive a monetary incentive at each study visit, as well as condoms, counseling, and linkages to survivor resources.

**12.3 Safeguards to protect any recognized vulnerability of the study participants**

Only staff and interviewers trained in specimen collection and discussion of sensitive sexual behavior will be used in the proposed study. Also, to secure an environment where the interviewee will be secure the information is kept confidential. Personally identifying information (e.g., names) is not transmitted with specimens. Confidentiality of PLHIVs will be safeguarded by only using HIV support groups and HIV counselors (therefore, people

already known to the PLHIV) to communicate with them prior to enrolment of the study. The counselling script for women includes questions to recognize intimate partner violence and offer referral if the participant is experiencing this.

**12.4 Reimbursement or compensation to study participants**

Participants will receive compensation at the initial visit and again at every subsequent

follow-up visit. Determination of the compensation amount follows: 50,000 Leones will be for attending a study visit, an additional 50,000 Leones will cover transportation costs of the participant, and 20,000 Leones will cover the costs of a meal. The total amount that a participant will receive at each visit will be 120,000 Leones. (Participants may choose to spend their compensation as they wish.) At every visit, 5 weeks’ worth of condoms (approximately 35 condoms) will be given to the participant, as well as formula as needed to breast feeding women. Participants will receive compensation for attending a study visit even if they do not complete a study visit (e.g. incomplete interview or specimen collection). Participants who do not complete multiple study visits may be deemed ineligible from participating further.

**12.5 Access to treatment or counselling for conditions either identified during screening of potential participants or resulting from the study intervention**

Participants will be offered timely risk reduction counseling on prevention of transmission of EBOV by trained counselors. In addition, all participants in need of specific health services (including physical or mental health, participants experiencing intimate partner violence, or breastfeeding women whose breast milk tests positive and need alternative sources of nutrition for their babies) will be referred to the appropriate clinic/hospital for care and management. HIV positive participants will be referred to the national program including HIV counseling and treatment services.

